## Introduction

Hyperkalaemia is a potentially life-threatening electrolyte disorder associated with cardiac arrhythmias and cardiac arrest [1]. Insulin–dextrose therapy (IDT) remains the mainstay of acute management, promoting intracellular potassium uptake *via* stimulation of the Na^+^–K^+^–ATPase pump. Despite co-administration of dextrose, IDT carries a significant risk of iatrogenic hypoglycaemia, with an estimated incidence of 17.2% [2]. Locally, rates as high as 30% have been observed, including 6.7% classified as severe hypoglycaemia [3].

The regimen of 10 units of short-acting insulin co-administered with 25 g of glucose has remained the standard of care for decades, despite being derived primarily from small studies in haemodialysis populations [4]. There is broad agreement that this regimen warrants re-evaluation to minimise the risk of iatrogenic hypoglycaemia. Some studies have found that lower dose insulin (<10 units) reduces hypoglycaemia risk without compromising potassium-lowering efficacy, while others have demonstrated a diminished biochemical response and no difference in hypoglycaemia [2,5]. Dextrose dosing is similarly conflicting, but doses exceeding 25 g may be associated with a lower risk of hypoglycaemia [5]. The delivery method also appears important with some research suggesting a reduced risk of hypoglycaemia when dextrose is provided as a sustained infusion rather than bolus administration [2]. Most of this evidence is derived from retrospective studies, and to date, no randomised controlled trials (RCT) have directly examined the optimal insulin-to-glucose ratio for the management of hyperkalaemia.

In the absence of a definitive ratio, clinicians must instead rely on patient-specific risk factors to guide therapy. Lower pre-treatment blood glucose level (BGL) is the strongest predictor of hypoglycaemia following IDT, with non-diabetic patients particularly susceptible [2,6,7]. Other potential risk factors include renal insufficiency, older age and lower body weight [6].

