### Intervention

Participants will be allocated *via* stratified (potassium <6.5 mmol/L [117 mg/dL] or ≥6.5 mmol/L [117 mg/dL), block randomisation to receive either glucose-only therapy or insulin–dextrose therapy (IDT) in a 1:1 ratio with the use of sequential, opaque, sealed envelopes. Envelopes are opened by members of the research team or clinical pharmacists only after formal participant enrolment is confirmed and documented. Interventions will be prepared by the same staff who open the envelope and away from clinical areas. Study solutions will appear visually identical to ensure blinding of participants and treating clinicians. The study period extends for six hours following randomisation. In eligible participants, treatment commences as soon as possible after enrolment.

In the glucose-only arm, participants will receive 100 mL of 50% dextrose administered over 10 min, followed immediately by 250 mL of 10% dextrose infused over two hours.

In the insulin–dextrose arm, participants will receive 10 units of intravenous insulin (Actrapid) mixed with 50 mL of 50% dextrose and 50 mL of 0.9% sodium chloride (total 100 mL), administered over 10 min, followed by 250 mL of 0.9% sodium chloride infused over two hours.

Infusion bag 1 (100 mL) will be prepared by modifying 0.9% sodium chloride bags according to the assigned intervention. Study labels will be affixed to the front of each bag. Infusion bag 2 (250 mL) will consist of the proprietary product used in each arm without alteration; these bags will be concealed using an opaque black sleeve to mask product identity, with study labels applied to the exterior.

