## Statistical considerations

The target sample size for this study is 95 enrolments (approximately 48 per treatment arm). This sample size was primarily determined to provide 80% power to detect a statistically significant difference in the incidence of hypoglycaemia, assuming an incidence of 17% in the IDT group and 0% in the glucose-only group, using a two-sided significance level (α) of 0.05.

To account for repeat enrolments (maximum of two per participant), a design effect of 1.1 was applied. This was derived from an assumed intra-class correlation coefficient (ICC) of 0.3 and an average of 1.2 enrolments per participant. The ICC was conservatively selected to reflect potential within-subject correlation in hypoglycaemia risk. The final figure of 95 enrolments includes a 10% buffer to account for attrition or missing data (e.g. missed blood glucose measurements or haemolysed potassium samples).

This sample size also provides sufficient power for the primary non-inferiority objective serum potassium reduction at two hours. With a non-inferiority margin of −0.5 mmol/L (–9 mg/dL), an assumed true mean difference of 0.0 mmol/L and a standard deviation of 0.8 mmol/L (14.4 mg/dL), a minimum of 82 enrolments is required to achieve 80% power (α = 0.025, one-sided). Thus, the planned recruitment of 95 enrolments ensures the study is adequately powered for both primary endpoints.

All analyses will adhere to a modified intention-to-treat (mITT) principle, including participants who are randomised, receive the assigned intervention, and have at least one post-baseline potassium and BGL measurement. For participants commencing dialysis within the 6-hour observation period, data up to the point of dialysis initiation will be included. Per-protocol analyses will be undertaken as sensitivity analyses to assess potential bias arising from treatment cross-over (patients in the glucose only group receiving insulin).

For the primary safety outcome (hypoglycaemia incidence), proportions will be summarised by treatment group, and the between-group difference will be reported with 95% confidence intervals (CI). Groups will be compared using Fisher’s exact test. If clustering due to repeat enrolments is evident, a generalised linear model with a binomial error structure and robust standard errors adjusted for clustering will be used.

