For the primary efficacy outcome (change in serum potassium at two hours), mean (SD) reductions in each group and the between-group mean difference (95% CI) will be reported. Non-inferiority will be concluded if the lower bound of the 95% CI is greater than −0.5 mmol/L (–9 mg/dL).

Secondary outcomes will be summarised descriptively by treatment group. To compare groups, general linear models will be calculated with an identity or binomial error structure for continuous or categorical outcomes. Group differences will be reported as mean differences (continuous) and risk differences or risk ratios (categorical) with 95% CIs. Repeated measures data will be analysed using linear mixed-effects models, which account for within-subject correlation and accommodate missing data.

Missing data will be managed based on the extent of data loss. If missingness is minimal (<5%), cases with missing data will be excluded from analysis. Potassium results from haemolysed samples will be counted as missing data. Mixed-effects modelling will allow the inclusion of all available data, mitigating bias related to incomplete measurements.

No adjustment for baseline covariates is planned, as randomisation is expected to achieve balance between treatment groups. A two-sided p-value of <0.05 will be considered statistically significant. All analyses will be performed using an appropriate statistical software package.

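### The primary hypoglycaemia test leaves out baseline glucose on the ground of expected balance; an exact test stratified by glucose would be more powerful, though most of the gain comes from relieving Fisher's discreteness

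*Protocol article*

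**What the plan says.** All references are to the protocol article.

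- **Test.** Statistical considerations fixes an unstratified Fisher's exact test for hypoglycaemia ("Groups will be compared using Fisher"). A binomial model with cluster-robust standard errors replaces it if clustering from repeat enrolments is evident. No covariate is named for either.
- **Adjustment.** The same section says: "No adjustment for baseline covariates is planned, as randomisation is expected to achieve balance between treatment groups".
- **Predictor.** The Introduction says that lower pre-treatment blood glucose "is the strongest predictor of hypoglycaemia following IDT, with non-diabetic patients particularly susceptible". It gives no effect size.
- **Availability.** Table 1 uses pre-treatment glucose for eligibility (diabetes and values above 7.8 mmol/L are excluded), and Table 2 schedules it at baseline.
- **Randomisation.** Under Intervention, the only stratification factor is potassium, below versus at or above 6.5 mmol/L.
- **Sample size.** The calculation rests mainly on this endpoint and aims for 80% power, with these inputs: "assuming an incidence of 17% in the IDT group and 0% in the glucose-only group, using a two-sided significance level (α) of 0.05". The target is 95 enrolments, about 48 per arm, after a design effect of 1.1 and a 10% buffer.

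**The concern.** The reason given for not adjusting does not support the choice. Balance in expectation does not rule out chance imbalance in 95 enrolments, and randomisation is not stratified by glucose. More importantly, the main purpose of adjusting for a strong predictor in a randomised trial is precision, which is available whether or not the arms happen to balance.

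The outcome is itself a threshold on glucose, and its baseline value costs nothing extra to collect. This endpoint drove the sample size. The section on trial feasibility says the target is close to the number of eligible presentations expected over two years, so lost power could hardly be bought back by recruiting more. The analysis is where efficiency can still be gained.

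**Working it through.** **1. Reproduce the stated 95.** Unpooled normal formula, 17% versus 0%, two-sided 0.05, 80% power:

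n = (1.960 + 0.842)² × 0.17 × 0.83 / 0.17² = 38.3, so 39 per arm and 78 in total.

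78 × 1.1 = 85.8; then × 1.1 = 94.4, or / 0.9 = 95.3. The stated figure reproduces.

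**2. Net sizes.** 95 × 0.9 = 85.5, about 43 per arm net of attrition. 85.5 / 1.1 = 77.7, about 39 per arm net of the design effect as well.

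**3. Fisher's power.** With no events on glucose-only, 5 versus 0 gives p of about 0.055 and 6 versus 0 about 0.026 at these sizes. Fisher's test therefore needs at least 6 events on IDT, and power is P(X ≥ 6) for X ~ Binomial(n, 0.17): 67.1% at 39 per arm, 76.2% at 43 and 84.8% at 48. It reaches 80% at 46 per arm. The shortfall at the net sizes comes from sizing with a normal formula and testing with a conservative exact test.

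**4. Exact test stratified by glucose.** Assumptions: enrolments independent apart from the reduced n, a median split of baseline glucose, zero events on glucose-only, and IDT rates by low/high glucose half averaging 17%. The article gives no strength of association, so a range is shown. The two-sided p sums all outcomes no more probable than the one observed. There were 40,000 simulated trials per cell.

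| Per arm | Fisher | Stratified, 17/17 (no glucose effect) | Stratified, 25/9 | Stratified, 30/4 | Unstratified test rejecting at 5 v 0 |
|---|---|---|---|---|---|
| 39 | 67.1% | 75.2% | 78.3% | 82.3% | 81.6% |
| 43 | 76.2% | 82.3% | 85.2% | 88.6% | 87.7% |
| 48 | 84.8% | 88.0% | 90.2% | 92.5% | 92.8% |

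The simulated size of the stratified test with equal arms at 43 was 2.8% to 3.6%, against 1.6% to 2.6% for Fisher's.

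**5. Split the gain.** Against Fisher's test simulated in the same scenario:

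- 39 per arm: 75.2 − 67.1 = 8.1; 78.3 − 67.5 = 10.8; 82.3 − 67.9 = 14.4 points.
- 43 per arm: 82.3 − 76.4 = 5.9; 85.2 − 76.7 = 8.5; 88.6 − 77.3 = 11.3 points.

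The first figure in each row has no glucose effect, so those 6 to 8 points come only from breaking up Fisher's coarse distribution. The part due to glucose is 78.3 − 75.2 = 3.1 to 82.3 − 75.2 = 7.1 points at 39 per arm, and 85.2 − 82.3 = 2.9 to 88.6 − 82.3 = 6.3 at 43.

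**6. Sensitivity to the p-value definition.** With a doubled one-tailed exact p, stratified power is about 71%, 73% and 75% at 39 per arm and 79%, 80% and 83% at 43. The total gain over Fisher's test is then only somewhere between 2 and 9 points. In a separate logistic simulation with odds ratios of 2 to 5 per SD of glucose, stratifying added about 2 to 5 points when mid-p was used both with and without strata. With the asymptotic tests (Cochran-Mantel-Haenszel against Pearson) it lost 1 to 2.

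**7. Chance imbalance.** With 43 per arm and a median split, the arms differ by at least 10 percentage points in the share with low glucose with probability 39%, and by at least 15 points with probability 20% (hypergeometric).

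**The case against.** The strongest counter-argument is that the planned test is valid, stated in advance and holds its error rate. With about seven expected events (0.17 × 43 = 7.3), leaving out covariates is defensible. That stands: this is a loss of efficiency, not an error of validity.

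A reader might infer from the 6 to 14 point gap that ignoring glucose costs that much power. The figures do not support this, because the lower end is the scenario in which glucose predicts nothing. Boschloo's unstratified test rejects at 5 versus 0 (p = 0.031, 0.040 and 0.035 at 39, 43 and 48 per arm). It matches or beats the stratified test except at the net sizes under the strongest association, where the two are within about 1 point.

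The predictor's strength is also assumed. The 25/9 and 30/4 splits imply odds ratios between halves of (0.25/0.75)/(0.09/0.91) = 3.4 and (0.30/0.70)/(0.04/0.96) = 10.3. Excluding diabetes and glucose above 7.8 mmol/L narrows the predictor's range, so the upper end may be optimistic.

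Finally, an exact stratified test assumes independent enrolments, as Fisher's does, so the cluster-robust fallback needs its own provision. A separate analysis plan may exist, but the article itself fixes both the test and the no-adjustment rule, so the point does not rest on missing detail.

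**Conclusion.** The point holds as a modest, nearly free improvement. Expected balance does not justify leaving out the predictor that the article itself ranks first. Fisher's test has about 67% to 76% power at 39 to 43 per arm, against the stated 80%; with all 48 per arm evaluable it has 85%. A probability-ordered exact test stratified by baseline glucose has about 75% to 89% at the net sizes. Of the difference, 6 to 8 points come from relieving discreteness and about 3 to 7 from glucose. These figures rest on 17% versus 0%, a median split, the assumed 25/9 to 30/4 associations, and clustering handled only through the reduced n.

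**What to change.** In Statistical considerations, before unblinding:

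1. Make the primary hypoglycaemia test an exact conditional (Cochran-Mantel-Haenszel type) test stratified by baseline glucose at one fixed cut, for example the blinded pooled median.
2. Name the two-sided p-value definition: probability-ordered or mid-p. Mid-p does not guarantee the 5% level, although its simulated size stayed at or below about 4%.
3. Keep the unadjusted risk difference with 95% CI, and Fisher's test, as sensitivity analysis.
4. Drop the expected-balance rationale for this endpoint.
5. Include baseline glucose in the fallback for clustering, and use a method that tolerates zero events in one arm, such as penalised likelihood or a permutation test that respects repeat enrolments. An ordinary adjusted logistic model would face separation.

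The cost is wording and one standard procedure, with no new data. The cut and p-value definition must be fixed in advance, and the stratified p-value may occasionally disagree with the unadjusted interval. If the investigators prefer no covariate, an unstratified, less conservative exact test such as Boschloo's recovers a similar amount of power, but it does not protect against chance imbalance in glucose.

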### Outcomes

The primary safety outcome is the incidence of hypoglycaemia (blood glucose <3.9 mmol/L (70 mg/dL), within 6 h post-treatment). Blood glucose is measured using validated bedside point-of-care glucometers. The primary non-inferiority outcome is the mean change in serum potassium (mmol/L) from baseline to 2 h post-treatment. Note that if a patient is enrolled based on a blood gas result due to clinical urgency, only the contemporaneous serum sample will be used for analysis. Secondary outcomes are severity of hypoglycaemia (ADA criteria); incidence of infusion-related complications including thrombophlebitis and extravasation; proportion of participants requiring rescue insulin therapy within 6 h post-treatment; mean change in serum potassium from baseline at 1 h and 4–6 h post-treatment; proportion of participants achieving a clinically significant potassium reduction (≥0.5 mmol/L [9 mg/dL] within 2 h); presence and resolution of hyperkalaemic ECG changes; serum insulin and C-peptide concentrations at baseline, 1 h, and 2 h post-treatment.

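### Randomisation is stratified by potassium, but the primary potassium comparison is planned without baseline adjustment; the analysis is valid but may be less precise than it need be

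*Protocol article*

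**What the plan says.** The Intervention section describes allocation as "stratified (potassium <6.5 mmol/L [117 mg/dL] or ≥6.5 mmol/L [117 mg/dL), block randomisation to receive" one of the two treatments, "in a 1:1 ratio with the use of sequential, opaque, sealed envelopes". Potassium is the only stratification factor named.

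Under Outcomes, "The primary non-inferiority outcome is the mean change in serum potassium (mmol/L) from baseline to 2 h post-treatment". Under Statistical considerations, the analysis of that outcome is that "mean (SD) reductions in each group and the between-group mean difference (95% CI) will be reported", with the decision rule "Non-inferiority will be concluded if the lower bound of the 95% CI is greater than −0.5 mmol/L". The same section then states: "No adjustment for baseline covariates is planned, as randomisation is expected to achieve balance between treatment groups".

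Linear mixed models are mentioned there for repeated-measures data and in connection with missing data. They are given no baseline or stratum term and are not clearly assigned to the primary comparison.

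**The concern.** The design treats potassium as important enough to stratify on, and the analysis then leaves it out. The reason given is balance. Balance bears on bias, whereas the main purpose of adjusting for a prognostic baseline value is precision. When allocation is stratified on a factor that predicts the outcome, the true sampling variance of the treatment difference falls, but an unadjusted standard error does not reflect this.

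A change score does not settle the matter. It subtracts baseline with a fixed slope of 1, so any remaining relation between baseline and change stays in the residual. Participants are selected for potassium above 5.5 mmol/L, so some relation through regression to the mean is plausible, although the article does not report one.

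Non-inferiority is decided by one confidence limit. An interval wider than necessary makes it more likely that a truly non-inferior treatment fails the test.

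**Working it through.** **Inputs from Statistical considerations.** Margin 0.5 mmol/L, SD of change 0.8 mmol/L, true difference 0, one-sided α 0.025, power 80%, stated minimum 82 enrolments, target 95, allowance for loss 10%.

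**Input not in the article.** The correlation r between baseline potassium and the size of the 2 h fall. It is assumed, and shown from 0 upward.

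**Step 1: the plan's own figure.** n per arm = 2 × (0.8 × (1.960 + 0.842) / 0.5)² = 40.19, rounded up to 41, so 82 in total. The stated figure is reproduced for an unadjusted analysis.

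**Step 2: numbers available.** 95 × 0.9 = 85.5, about 86, or 43 per arm.

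**Step 3: unadjusted power.** Φ(0.5 / (0.8 × √(2/43)) − 1.96) = Φ(2.898 − 1.96) = Φ(0.938) = 82.6%. The exact t calculation gives 81.7%. Hence about 82%.

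**Step 4: adjusted power by formula.** Adjusted SD = 0.8 × √(1 − r²), put into the same expression.

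**Step 5: simulation.** There were 4,000 trials per setting with N = 86, strata cut at 6.5 mmol/L, an assumed block size of 4, an assumed skewed baseline (5.5 plus a gamma variable, mean 6.4, SD 0.64), change SD 0.8, and no repeat enrolments.

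| r | Adjusted SD | Power by formula, adjusted | Simulated power: none / stratum only / continuous baseline | Mean 95% half-width: none / continuous baseline |
|---|---|---|---|---|
| 0 | 0.800 | 82.6% | 82.0 / 81.9 / 81.8% | 0.342 / 0.342 |
| 0.3 | 0.763 | 85.9% | 82.2 / 83.6 / 85.3% | 0.343 / 0.328 |
| 0.5 | 0.693 | 91.7% | 83.3 / 86.8 / 90.1% | 0.343 / 0.297 |
| 0.7 | 0.571 | 98.2% | 85.7 / 93.1 / 97.9% | 0.343 / 0.245 |

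The Monte Carlo standard error near 82% is √(0.82 × 0.18 / 4000) = 0.6 points. The analyses were compared on the same simulated trials.

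**Step 6: is the unadjusted interval conservative?** At zero true difference its simulated coverage was 94.4% (r = 0), 95.8% (0.3), 96.7% (0.5) and 98.2% (0.7). With the true difference at the margin, its type I error was 2.5%, 2.4%, 1.9% and 1.0% against a nominal 2.5%. Continuous adjustment gave coverage between 94.4% and 95.1%.

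The simulation fitted the stratum and continuous baseline in separate models. The model proposed under the fix holds both, a combination that was not simulated.

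**The case against.** The strongest reply is that nothing here is an error. The unadjusted test is valid, its conservatism lowers the chance of a false claim of non-inferiority, and the sample size calculation is right for the analysis described. All of that stands. The point concerns efficiency.

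It might also be said that an analysis plan not shown could add the adjustment. But the article states a decision and a reason for it, and a plan that adjusted would contradict that sentence.

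A reader might infer more than the article supports:

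- *That the estimate is biased, or that chance imbalance passes straight into it.* Randomisation protects against bias. Stratified blocks limit imbalance on this variable, and subtracting baseline removes part of what remains.
- *That the trial has no power to spare.* Dividing also by the 1.1 design effect gives 95 × 0.9 / 1.1 / 2 = 38.9, about 39 per arm, with 79% power and a half-width of 0.355. But that design effect was set for hypoglycaemia, and its stated inputs give 1 + (1.2 − 1) × 0.3 = 1.06. Carrying it over to potassium is an assumption.
- *That a sizeable gain is assured.* A correlation of 0.3 to 0.7 between baseline and 2 h values, with equal SDs, would raise that 79% to between 93% and 85%. This choice implies a baseline-change correlation of magnitude √((1 − 0.3)/2) = 0.59 to √((1 − 0.7)/2) = 0.39. It therefore leaves out the weak correlations at which little is gained. It is also a different quantity from r in the table.
- *That every participant has a usable baseline.* Haemolysed potassium results count as missing, and the modified intention-to-treat definition asks for a post-baseline potassium only. Such participants lack a change score under the current plan too, so adjustment need lose nobody further.

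**Conclusion.** The point holds as one of efficiency. Expected balance does not justify leaving out baseline potassium, and the unadjusted interval is wider than necessary whenever change depends on baseline.

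At about 43 per arm the gain in power from continuous adjustment is nil at r = 0, about 3 points at r = 0.3 (85% against 82%) and about 7 points at r = 0.5 (90% against 83%). At r = 0 the cost in power is negligible. These figures rest on the protocol's SD of 0.8 and zero true difference, on an assumed r, and on the assumed baseline distribution and block size. The article cannot show which r applies.

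The change is worth making because it costs little and acts on the limit that decides the trial. It does not mean that the present analysis is invalid or that the stated 82 enrolments are wrong. It concerns the potassium outcome only; covariate adjustment is less straightforward for hypoglycaemia, where one arm is assumed to have no events.

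**What to change.** For the potassium outcome, replace the sentence on baseline covariates. Take the primary estimate from a linear model for the 2 h value with treatment, continuous baseline serum potassium and the randomisation stratum. Alternatively, use a mixed model on the 1 h and 2 h values with treatment-by-time and the same baseline terms, so that a participant with a haemolysed 2 h sample still contributes the 1 h value.

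Specify also:

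- the stratum as used at allocation, since enrolment may rest on a blood gas or a serum result;
- standard errors that allow for up to two enrolments per participant;
- the difference expressed as reduction on glucose-only minus reduction on insulin–dextrose, so that the lower-bound rule against −0.5 mmol/L keeps its direction (a difference in 2 h levels has the opposite sign);
- a simple rule for the few participants whose baseline sample is haemolysed;
- the unadjusted difference as a supportive analysis.

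Baseline, 1 h and 2 h serum potassium are already scheduled in Table 2, so no new data are needed. The cost is an amendment to the protocol and registry wording, made before unblinded data are seen.
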